### **3.2 Study population**

The study population is food handlers of the working-age between 19-65 years old, B40 category, in Selangor, Malaysia.

### **3.3 Sampling population**

#### **3.3.1 Sampling unit**

Sampling unit in this study is a registered food handler in Selangor under municipal in the working-age between 18-65 years old involved in the research and individually answers the questionnaire.

#### **3.3.2 Inclusion criteria**

The inclusion criteria are:

- I. Malaysian citizen.
- II. Working in Selangor, registered with municipal council
- III. Involve in food and beverages industry.
- IV. Age 18-65-year-old.
- V. Consented to participate in the study

#### **3.3.3 Exclusion criteria**

The exclusion criteria are:

- I. Unable to read and write in Malay language and English

### **3.4 Sampling frame**

All food handlers of the legal working age between 19-65 years old, B40 category, in Selangor, Malaysia.

### 3.5 Sampling technique

There are 324 Food Handler Training Schools in Selangor located in nine districts. This study will use a simple random sampling technique to select the sampling location. Four districts will be randomly selected. Once the district is determined, the selection of the Food Handler Training School within the district will proceed by using a similar method and subsequently assigned. The flow of the sampling technique is shown in the figure below:

[figure not shown]

Figure 5. Cluster random sampling flow chart.

Cluster randomization will be used to ensure administrative efficacy, lessened risk of experimental contamination, and enhancement of subject compliance. The participants attending the food handler training program will be invited into the study via invitation and assessed for eligibility. The unit of randomization will be on a 1:1 basis in either the control or intervention group.

An independent research staff, blinded as to whether they were nominating within the control or an intervention group and unaware which of their participants had consented to participate.

[figure not shown]

Figure 6. Proposed research Flow Chart

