### **3.2 Study design**

The study is a randomized controlled trial study. A single blinded, cluster randomized controlled trial study design will be conducted with pre-assessment and post-assessment on the intervention module. The respondents will be divided into two groups, intervention or control. The control group will receive a standard treatment and brochures related to occupational safety and health, while the intervention group will receive a theory-based intervention module on occupational safety and health among food handlers. The duration of the study is within 3-6 months.

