**INTERVENTION MODULE OUTLINE**

**FIRST SESSION (1 HOUR)**

**MAIN OBJECTIVE:**

1. To enhance self efficacy among food handlers on occupational safety and health at food premise

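### Section 3.5 does not ensure that consent and baseline are complete before a school's arm is known, so enrolment could depend on the arm

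*Combined protocol and SAP*

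**What the plan says.** Section 3.5 (Sampling technique) draws four districts at random. It then says that "the selection of the Food Handler Training School within the district will proceed by using a similar method and subsequently assigned". Next comes recruitment: "The participants attending the food handler training program will be invited into the study via invitation and assessed for eligibility". The sentence after that reads "The unit of randomization will be on a 1:1 basis in either the control or intervention group". The section ends with a sentence about independent research staff who are "blinded as to whether they were nominating within the control or an intervention group" and who do not know which participants consented. That sentence has no main verb, so the staff's task is not defined.

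Other relevant places:

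- Section 3.3.2 makes consent an inclusion criterion (item V).
- Section 3.9 places consent before the study begins, and Section 3.12 places it before the questionnaire is answered. Neither relates it to allocation.
- Section 3.2 calls the design single blinded without saying who is blinded.
- On content, Section 3.2 says "The control group will receive a standard treatment and brochures related to occupational safety and health". The intervention module outline lists three sessions of one hour each.

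**The concern.** Randomising schools protects the comparison only if the individuals who enter do so without regard to the arm. If a school's allocation is known when its attendees are invited, two groups can act on it: attendees deciding whether to join, and school staff or trainers deciding whom to encourage or how to describe the study. The arms may then differ in ways that randomisation of schools does not control, such as interest in safety training.

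The outcomes are open to this. Attitude is rated on Likert items and practice is self-reported (Section 3.13). A bias from selective enrolment does not shrink as more participants are added, and it cannot be undone after enrolment. Without counts of those approached, eligible and consenting, it cannot even be assessed.

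**Working it through.** **1. The plan's figures.** The plan gives no uptake or consent rate by arm, so there is no figure to reproduce on this point. The sample size in Section 3.6 can be checked in part: 6 / (1 − 0.20)³ = 11.72, rounded up to 12 per cluster, and 20 × 12 = 240. It does not depend on the order of recruitment and is unaffected.

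**2. Order of events.** Section 3.5 mentions, in sequence, selection and assignment of schools, invitation and eligibility, the 1:1 allocation, and the blinded staff. Read in that order, a school is assigned before its attendees are approached. No sentence states this outright. Sections 3.9 and 3.12 fix consent relative to the study and the questionnaire, not relative to allocation. So no section we can read places consent and baseline before the arm is known.

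**3. Who is covered by blinding.** The Section 3.5 sentence covers staff while nominating. Because they are unaware of who consented, the consent step appears to lie outside what they do. Attendees, school staff, trainers and whoever assesses eligibility are not mentioned by role.

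**4. What the analysis would remove.** Section 3.6.1 defines the primary outcomes as changes in mean knowledge and attitude scores. Take a trait held by a share q_I of intervention enrollees and q_C of control enrollees. Let it shift the score by d0 SD at baseline and d1 SD at follow-up, with no intervention effect:

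- bias in the follow-up level = (q_I − q_C) × d1
- bias in the change = (q_I − q_C) × (d1 − d0)

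The second line is zero if enrolment does not depend on the arm (q_I = q_C), and also if the trait's effect is stable over time (d1 = d0). It is not zero when the trait alters how much people learn or how they report after training.

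**5. Illustration on assumed inputs.** None of these inputs is in the documents. Suppose half of attendees hold the trait and control schools enrol 70% of both kinds, so q_C = 0.5.

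- Intervention enrols 80% with the trait and 60% without: q_I = 0.8/1.4 = 0.571, difference 0.071.
- Intervention enrols 90% and 50%: q_I = 0.9/1.4 = 0.643, difference 0.143.
- If d1 − d0 = 0: bias in change is 0 in both cases.
- If d1 − d0 is 0.3 SD in either direction: 0.071 × 0.3 = 0.02 SD and 0.143 × 0.3 = 0.04 SD, with the same sign as d1 − d0.
- If it is 0.8 SD in either direction: 0.06 SD and 0.11 SD.

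The sign is open. Keener enrollees may learn more (d1 > d0). Enrollees who already score high have less room to gain on a bounded scale (d1 < d0); the attitude total, for instance, stops at 15 (Section 3.13).

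**6. Covariates.** Sections 3.6.2 and 3.10 list age, gender, ethnicity, education, employment status, income, work experience and previous training. Objective 4 controls for covariates. None of these measures motivation or reporting style.

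**The case against.** The strongest reply is that the plan never says allocation is known at invitation. The word for assigning schools names neither an arm nor a time, and the only sentence that mentions control or intervention allocation comes after the invitation sentence. Figures 5 and 6 and the information sheets could settle the matter and are not available to us, so their absence cannot be held against the plan. This stands. A reader might infer that the protocol prescribes recruitment after the arm is revealed; the documents support only that the readable text does not rule it out.

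Second, if single blinded means that participants are blinded, the route through attendees' own choice largely closes. That is possible, but Section 3.2 does not say so. Nor can one say that the nominating-staff sentence is the plan's only safeguard, or that the eligibility assessor is unblinded, since that person may be among the blinded staff.

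Third, a reader might infer that the intervention is the heavier commitment and that the bias therefore favours TRIM-OSH. Section 3.1 hints that the safety training is additional to the compulsory course, but no duration is given for the control training, and the module may be delivered partly online. Neither the burden gap nor the direction is established.

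Fourth, one might be tempted to attach a size. If 30% of attendees were less motivated and scored 0.5 SD lower, and half of them declined only in intervention schools, the gap would be (0.30 − 0.15/0.85) × 0.5 = 0.06 SD; if all declined, 0.30 × 0.5 = 0.15 SD. The arithmetic is right, but these are differences in score level. In the change scores that define the primary outcomes they cancel if stable over time, so they are no estimate of the bias here.

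Last, baseline KAP and characteristics are compared between arms and covariates are adjusted for. That would reveal or reduce measured imbalance, but not differences in learning or later self-report.

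**Conclusion.** The concern holds in a limited form. The plan as readable does not ensure that consent and baseline come before the arm is known to school staff, trainers or attendees, and its blinding sentence is incomplete and confined to nominating staff. Enrolment could therefore depend on the arm through attendees' or schools' choices. The planned covariates and change scores would deal with measured or stable differences, but not with differences in how much enrollees learn or how they report after training.

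The size and direction of any bias cannot be derived from the documents; with effective blinding of recruiters and attendees it would be zero. The conclusion rests on reading Section 3.5 in the order written and would fall away if the flow charts or information sheets show that consent and baseline precede disclosure. The sequence should be fixed before enrolment starts.

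**What to change.** In Section 3.5:

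1. State that, within each selected school, invitation, eligibility assessment, consent and the baseline questionnaire are completed before that school's allocation is disclosed to school staff, trainers and participants. Use the same neutral information about the study in both arms.
2. Complete the blinding sentence: what the independent staff do, and who is blinded at invitation, eligibility assessment, consent and outcome assessment. Align the single-blind description in Section 3.2 with it.
3. Record the numbers approached, eligible and consenting per school, and report them by arm.

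The cost is protocol wording, an allocation list held centrally or sealed, and simple recruitment logs. The one practical downside is that trainers must be ready to deliver either programme until allocation is opened after baseline. No extra participants are needed.

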### 3.6 Sample size

The sample size calculation in this study was based on the targeted primary outcomes, such as knowledge, attitude, and practice of safety and health. A previous power analysis specified an enrolment target of 20 clusters of six participants per condition. Provided that the average attrition rate in previous intervention studies was 20%, conservative estimation will be conducted on the attrition at 20% for each testing time point when the target sample size is designed. Given that the total time points in this study requirement are three times follow up after the baseline data collection, the required sample size comprises 20 clusters of 12 participants per group ( $N = 240$ ). To encourage retention, lottery-style drawings will be carried out for participants who complete each data

collection phase. Retention bonus pay will be offered for those who complete all four data collection phases.

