**Result:**

A total of 139 participants expected to be finally selected to participate in the study with response rate of more than 80%. At baseline, the characteristics of the sociodemographic, socioeconomic, working experience and training attendance of food handlers hypothesized to show no difference in between group. It is hypothesized that there will be a significant improvement on knowledge, attitude and practice (KAP) on occupational safety and health at food premises among food handlers in the intervention group compared to the control post training and 1 month follow up. In the GLMM analysis, it is hypothesized that the TRIM-OSH is associated with improving KAP among food handlers on occupational safety and health at food premises.

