### **3.9 Data collection methods**

The data collection will occur in the selected districts in Selangor, Malaysia, within a given time frame. The questionnaire will be distributed to selected respondents in the selected Food Handler Training School. All participants who agree to participate in the study will be consented by agreeing to the agreement statement prior study begins. The questionnaire will be given in the Google Form format for the participants to access the form with the response collected immediately upon completion before and immediately after training. The participants will be contacted after one-month post-training for the reassessment of the KAP score. If the accessibility of the Google Form is not available, the same questionnaire in the hardcopy format will be given and collected on the same day at all mentioned events.

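### Section 3.6 inflates the sample for three follow-ups and ties a bonus to four data-collection phases, but the readable schedule has two follow-ups and three phases

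*Combined protocol and SAP*

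**What the plan says.** Section 3.6 (Sample size) starts from an earlier calculation: "A previous power analysis specified an enrolment target of 20 clusters of six participants per condition". It then allows for loss: "conservative estimation will be conducted on the attrition at 20% for each testing time point". The number of time points is given as follows: "the total time points in this study requirement are three times follow up after the baseline data collection". The result is that "the required sample size comprises 20 clusters of 12 participants per group", with N = 240 in brackets. On incentives, the section offers lottery draws to those who complete each phase, and adds: "Retention bonus pay will be offered for those who complete all four data collection phases".

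Section 3.9 (Data collection methods) describes the assessments themselves. The questionnaire is given "with the response collected immediately upon completion before and immediately after training", and then: "The participants will be contacted after one-month post-training for the reassessment of the KAP score". That makes a baseline and two follow-ups. Objective 4 in section 1.5.2 and the Result paragraph of the executive summary name the same two follow-ups. Dummy Tables B to F in section 4.1 have only baseline, post-intervention and 1-month.

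**The concern.** The number of follow-ups feeds directly into the inflated cluster size, so a count that disagrees with the schedule leaves the stated requirement resting on visits the trial does not describe. Three follow-ups after baseline and four phases are the same count, so section 3.6 is consistent with itself. This is not a slip in one word, nor a count of follow-ups that happens to include the baseline.

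Two things are at stake. The stated cluster size does not follow from the readable schedule. And a payment to participants has a condition that the readable schedule does not let anyone meet.

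**Working it through.** **Inputs.** From section 3.6: base size n = 6 per cluster; loss d = 0.20 at each testing time point; k = 3 follow-ups; 20 clusters. From section 3.9, Objective 4, the executive summary and Tables B to F: k = 2 follow-ups.

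**Reproducing the plan's figure.** Section 3.6 gives no formula. Compounded loss, n/(1 − d)^k, fits:

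- 6/0.8^3 = 6/0.512 = 11.72, rounded up to 12 per cluster
- 20 × 12 = 240

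Other ways of applying 20% three times to six per cluster do not give 12:

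- 6 × 1.2^3 = 10.4, rounded up to 11
- 6 × (1 + 0.6) = 9.6, rounded up to 10
- 6/(1 − 0.6) = 15

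Inflating the total instead of the cluster gives 120/0.512 = 234.4, so 235, which is close to 240 but not equal to it. Compounding per cluster is therefore the likely rule, though it is inferred.

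**The same rule with the scheduled follow-ups.**

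- 6/0.8^2 = 6/0.64 = 9.375, rounded up to 10 per cluster
- 20 × 10 = 200
- Excess: 240 − 200 = 40, and 40/200 = 20%

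If the plan means 20 clusters in each of two groups, the totals are 40 × 12 = 480 and 40 × 10 = 400. The excess is again 20%.

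**Expected completers with two follow-ups.**

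- Enrol 12 per cluster: 12 × 0.64 = 7.7 per cluster; 240 × 0.64 = 153.6, about 154 in all
- Enrol 10 per cluster: 10 × 0.64 = 6.4 per cluster
- Target: 6 per cluster; 20 × 6 = 120 in all

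Both sizes meet the target.

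**Bonus.** Phases required: 4. Phases in the readable schedule: 1 baseline + 2 follow-ups = 3.

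**What cannot be checked.** The base of six per cluster cannot be reproduced, because the documents give no effect size, standard deviation, intracluster correlation or power.

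**The case against.** The strongest defence is that a fourth assessment may be intended. The research flow chart (Figure 6) is not shown in the text available, section 3.2 gives a study duration of 3 to 6 months, and the outcomes in section 3.6 (Variables) run to an endpoint that is not dated. This cannot be excluded. If it is so, 12 per cluster and the bonus both stand, and section 3.9, Objective 4 and the tables are incomplete. The contradiction remains either way.

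A second defence is that the error is harmless because it over-recruits. This stands as far as power is concerned, provided the 240 are actually enrolled.

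Some stronger readings are tempting, but the documents do not support them:

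- **Much larger excess.** A reader might assume that loss occurs only at one month, giving 6/0.8 = 7.5, so 8 per cluster, 160 in all and an excess of 80/160 = 50%. That replaces the plan's rule of 20% at every time point. Loss before the post-training form is also possible, as the module has three one-hour sessions.
- **Conflicting retention.** Three losses of 20% leave 0.8^3 = 51%, while the executive summary expects 139 people to be selected "with response rate of more than 80" per cent. That phrase is tied to selection and participation and need not mean completion of follow-up, so the two figures may not measure the same thing.
- **Retention damaged, or a promise broken.** The lottery draws still reward each phase, including the one-month contact, and nothing shows that the bonus is the main incentive. What participants are told about it is not visible, because the consent pages were removed before review.

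**Conclusion.** The point holds as an inconsistent input. It is not an error of arithmetic. Section 3.6 sizes the trial for three follow-ups, and every other readable statement of the schedule has two. On the plan's apparent rule, the cluster size is 12 where 10 would do: 240 against 200 on the 20-cluster reading, an excess of 20%. Taken alone this costs no power. As the schedule reads, the four-phase bonus cannot be earned.

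This rests on three assumptions: that loss compounds at 20% per follow-up, that the missing flow chart adds no assessment, and that the base of six per cluster is accepted as given. The 12-against-10 comparison does not depend on how the total is read. The totals do, and they are unsettled. Section 3.6 could mean 240 or 480, and the executive summary plans 139 participants, fewer than either 200 or 240.

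**What to change.** Decide how many assessments there are, and make every section agree.

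- **If three phases are intended:** change section 3.6 to two follow-ups. Then either restate the inflated size as 10 per cluster, or keep 12 and describe the excess as margin (about 7.7 expected completers per cluster against 6). Since the base of six cannot be verified, keeping 12 is the safer choice. Tie the bonus to all three phases, and check that this matches what participants are told.
- **If a fourth assessment is intended:** add it, with its timing, to section 3.9, Objective 4, the executive summary and the dummy tables. The figure of 12 then stands.

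In either case, write out the inflation formula, say whether the 20 clusters are in total or per group, and reconcile the total with the 139 participants in the executive summary.

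For the first option the cost is wording and one recalculation, plus any correction to the participant information on the bonus. The second adds a described visit to the schedule.

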**Methodology:**

The study is a single-blinded, cluster randomized controlled trial study, expected to be conducted from 1st December 2023 to 30th November 2024 among 139 registered food handlers in Selangor under municipal in the working-age between 18-65 years old. The respondents will be allocated into intervention and control group. The intervention group will receive TRIMOSH intervention while the control group will receive standard training. The data will be collected via self-administered questionnaires and has been analyzed using SPSS version 25.

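### The Executive Summary plans 139 participants, section 3.6 requires N = 240 under a label that could also mean 480 in total, and 139 falls short on every reading

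*Combined protocol and SAP*

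**What the plan says.** The Executive Summary gives the size twice. Its Methodology paragraph places the study "among 139 registered food handlers in Selangor under municipal" authority, to be split between intervention and control. Its Result paragraph says: "A total of 139 participants expected to be finally selected to participate in the study with response rate of more than 80" per cent.

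Section 3.6 (Sample size) builds a different figure in three steps:

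- Starting point: "A previous power analysis specified an enrolment target of 20 clusters of six participants per condition".
- Loss: "conservative estimation will be conducted on the attrition at 20% for each testing time point", where "the total time points in this study requirement are three times follow up after the baseline data collection".
- Result: "the required sample size comprises 20 clusters of 12 participants per group", followed by N = 240 in brackets.

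Section 3.2 (Study design) has two arms: "The respondents will be divided into two groups, intervention or control". Section 3.5 gives 1:1 allocation and four districts, but its readable text gives no number of schools.

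Specific objective 4 (section 1.5.2), section 3.9 and the dummy tables in section 4.1 show two assessments after baseline: at the end of training and one month later. Section 3.6 counts three, and offers a bonus for completing four data collection phases.

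Section 3.10 sets alpha at 0.05 for the analysis, without linking it to the sample size.

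**The concern.** Three totals can be taken from the current text: 139, 240 and 480. Someone planning recruitment, reviewing ethics or checking the final report would use a different target depending on the page. None of the figures comes with a derivation that shows what the trial could detect, so a reader cannot tell which number the design relies on.

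The choice matters most for the number of clusters. In a cluster-randomised trial, 10 or 20 clusters per arm are different designs, and section 3.6 can be read as either. The smaller figure of 139 matters because section 3.6 itself expects heavy loss and enlarges the sample to allow for it. A plan to enrol 139 would leave much of that allowance unfunded.

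**Working it through.** **1. Reproduce the plan's figure.** Inputs from section 3.6: 6 per cluster before loss, 20% loss at each time point, three follow-ups, 20 clusters.

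- Retention = 0.8³ = 0.512
- Enrolled per cluster = 6/0.512 = 11.72, rounded up to 12
- 20 × 12 = 240

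This matches N = 240. The inflation is correct.

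**2. What 240 counts.** With two arms:

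- 20 clusters in the whole trial (10 per arm): total 20 × 12 = 240. The words per group and per condition are then wrong.
- 20 clusters in each arm: 20 × 12 = 240 is one arm, and the total is 2 × 240 = 480.

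**3. Use the two follow-ups actually scheduled.** 6/0.8² = 9.4, rounded up to 10 per cluster. The total is 20 × 10 = 200, or 40 × 10 = 400.

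**4. Compare 139 with each reading.**

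| Reading | Total required | Shortfall at 139 |
|---|---|---|
| 20 clusters in all, two follow-ups | 200 | 61 |
| 20 clusters in all, three follow-ups | 240 | 101 |
| 20 clusters per arm, two follow-ups | 400 | 261 |
| 20 clusters per arm, three follow-ups | 480 | 341 |

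So 139 is 58% of 240 and 29% of 480. It is not a whole number of clusters of 12 (139/12 = 11.6). Inflating 120 does not produce it either: 120/0.8 = 150, 120 × 1.2 = 144, 120/0.8² = 188, 120/0.8³ = 235. If 139 were responders at 80%, enrolment would be 139/0.8 ≈ 174, still below 200.

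**5. Apply the plan's own loss to 139.** One follow-up: 139 × 0.8 = 111. Two: 139 × 0.64 = 89. Three: 139 × 0.512 = 71. The target before inflation is 20 × 6 = 120 on the smallest reading, or 240 with 20 clusters per arm.

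**6. Illustration of power.** The plan gives no effect size, SD, ICC or target power, so these are assumptions: ICC 0.05, two-sided 5%, an 80% target, a simple two-arm comparison of completers, noncentral t with df = clusters − 2, and effective n per arm = k·m/(1 + (m − 1)·ICC) for k clusters of m per arm.

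- Reference, 20 clusters × 6: effective n per arm = 60/1.25 = 48; 80% power at about 0.60 SD.
- 139 enrolled, power at that same difference:

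| Clusters in all | One loss | Two losses | Three losses |
|---|---|---|---|
| 20 (about 7 enrolled each) | 78% | 70% | 62% |
| 12 (about 12 enrolled each) | 68% | 61% | 54% |

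Over ICC 0.01 to 0.10, with 20 clusters and the reference difference recalculated for each ICC, the two-loss figure runs from 68% to 72% and the three-loss figure from 59% to about 65%.

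**The case against.** Much can be said for the plan. The arithmetic in section 3.6 is sound, so a reader who infers that 240 is miscalculated would be wrong: N may be the trial total, or it may be the size of one arm. The sampling and research flow charts are not shown in the text available here, and they may state the number of schools per arm. Section 3.6 is also the operative sample-size text, whereas 139 stands in a thesis-style abstract.

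A reader might infer that the trial will fail to deliver its required size, or that its power is known to be too low. The documents support neither. They contain no enrolment data, only conflicting planned sizes. As an enrolment figure, 139 exceeds 120 and drops below it only after loss. Counting completers at the last visit is strict, because the mixed model in section 3.10 can use people with partial follow-up. At the end-of-training comparison a single 20% loss gives about 78% in the illustration, close to the assumed 80%. The power figures also depend on how many clusters 139 is spread over, which the plan does not say.

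All of this stands, and it limits the claim. It does not remove the conflict: no readable text derives 139 or reconciles it with section 3.6, and the mixed model does not change a planned enrolment below the stated requirement.

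**Conclusion.** The point holds as a conflict between planned sizes together with an ambiguous label. The Executive Summary's 139 is below what section 3.6 requires on every reading: by 101 against 240, by 341 against 480, and by 61 or 261 if the inflation uses the two scheduled follow-ups. These comparisons use only the plan's own numbers. Whether 20 clusters means the trial or each arm is not settled by the readable text.

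The follow-up count is a second inconsistency inside the same calculation, because it determines whether 10 or 12 are enrolled per cluster. The basis of 20 clusters of six cannot be checked, since section 3.6 gives no effect size, SD, ICC or power and the alpha of 0.05 in section 3.10 is not tied to it. Whether clustering was allowed for is therefore unknown.

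The power values are illustrative and rest on the assumptions listed with them. They show the order of the possible loss, not the trial's actual power. The conflict should be resolved before the plan is relied on, since it leaves the recruitment target undefined.

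**What to change.** State one enrolment figure in the Executive Summary and section 3.6, written as clusters per arm × enrolled per cluster × 2 arms = total enrolled, followed by the total expected at the last follow-up. Then take the branch that applies:

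- **240 is the trial total:** state 10 clusters per arm, remove the per-group and per-condition wording, and correct 139.
- **20 clusters per arm is intended:** state a total of 480, and correct both N = 240 and 139.
- **139 is what will be enrolled:** delete the 240 requirement, and restate the detectable difference for 139 with its cluster count, ICC, alpha and power. Say openly that the difference was derived from the number and not the reverse.

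In each case, make the follow-ups in the inflation match the two scheduled. The plan's own method then gives 10 per cluster (200 or 400); if 12 is kept as a margin, say so. Give the effect size, SD, ICC, alpha and power behind 20 clusters of six.

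The cost is a text correction plus the work of recovering or choosing the missing inputs. The stated detectable difference may become less favourable. No extra enrolment is needed if the figure is restated for 139; if 240 or 480 is the real target, recruitment must be planned for that number.
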